## Abstract

**Background and Aims:**

Existing research on in‐person and virtual visitation is predominantly quantitative, focusing on the effectiveness and safety of these practices in the intensive care unit (ICU). Significant differences may exist in the experiences of diverse stakeholder groups regarding ICU visitation across these modalities. Consequently, we aim to explore the lived experiences of patients, family members, and healthcare providers with in‐person or virtual visitation practices in the ICU.

**Methods:**

A descriptive phenomenological qualitative study will be conducted to gain an insight into the in‐person or virtual visitation practices of the patients, family members, and healthcare providers. Participants will be recruited through purposive sampling from ICUs of three large public hospitals in Southwest China, focusing on stakeholders (patients, family members, and healthcare providers) involved in ICU family visitation. Sociodemographic information of participants will be collected. In‐depth individual interviews will be conducted using a semi‐structured interview guide until data saturation is achieved. The study will adhere to the Consolidated Criteria for Reporting Qualitative Research (COREQ). Data analysis will follow Colaizzi's seven‐step phenomenological method. NVivo 15 will be employed for data management and analysis.

**Discussion:**

This study is expected to uncover variations in implementation, elucidate stakeholder perspectives, identify challenges inherent to each approach, and ultimately advance the development of family visitation practices in ICUs.

## Introduction

1

The survival rate in the intensive care unit (ICU) has improved, but patients and their families remain at risk of experiencing significant psychological morbidity [1]. Research indicates that ICU survivors face a high risk of long‐term depressive symptoms [2], while family members frequently experience adverse psychological outcomes such as anxiety, depression, and post‐traumatic stress disorder [3], ultimately impairing their long‐term quality of life and health outcomes. Consequently, there is an urgent need for early interventions to mitigate the incidence of these conditions. Facilitating family presence in the ICU is a key strategy, as it promotes the communication between patients and their families, provides essential emotional support, helps to reduce the incidence of patient delirium and alleviate psychological distress among family members [4, 5].

In‐person visitation and virtual visitation are critical modalities for facilitating family presence in the ICU. Family presence is primarily facilitated through in‐person visitation, which is a crucial means of maintaining intimate connections and meeting emotional needs. However, such visitation is often restricted due to practical and safety concerns [6, 7, 8]. The COVID‐19 pandemic exacerbated these restrictions but also accelerated the widespread adoption of virtual visitation as an alternative [9, 10]. Nevertheless, there are significant differences in the standards for implementing virtual visitation across ICUs. Commonly targeted populations include alert and oriented patients or those at the end of life, while considerable debate persists regarding the appropriateness of virtual visitation for comatose or sedated patients [11]. Although virtual visitation has been shown to enhance the communication between patients and their families, alleviate psychological distress, and improve engagement in care or rehabilitation processes, it cannot fully substitute for in‐person visitation [8]. Challenges such as technological barriers, communication constraints, and staffing shortages further influence its effectiveness, contributing to current variability and uncertainty in practice [8].

Stakeholders—defined as individuals or groups responsible for or affected by family visitation decisions—primarily include patients, family members, and healthcare providers (clinicians, nurses, policymakers, and administrators), who play distinct yet critical roles in ICU family visitation practices [12]. Therefore, understanding stakeholders' experiences and needs is essential to address challenges across visitation modalities and improve family satisfaction [6, 13]. However, the existing quantitative studies on visitation have largely focused on describing the distribution and characteristics of ICU visiting policies [11, 14], identifying the factors influencing the implementation of visiting policy [10, 11], and evaluating the effects of visitation on patient physiological parameters and family psychological outcomes [4, 5, 15]. At the same time, existing qualitative inquiries have focused on clinical staff's perceptions of ICU visitation frameworks [16] and stakeholder perspectives (encompassing families and healthcare providers) regarding visitation paradigm shifts in the COVID‐19 context [17, 18, 19]. It is noteworthy that there is a lack of comparative analysis comparing the lived experiences of patients, family members, and healthcare providers across in‐person and virtual visitation modalities [20]. This important inquiry will facilitate the development of evidence‐based frameworks to guide the design and implementation of tailored family visitation programs.

## Aims

2

We aim to systematically explore and characterize the lived experiences of ICU stakeholders in both in‐person and virtual visitation modalities. Specifically, this study seeks to:

Explore the lived experiences and perspectives of stakeholders across different visitation modalities.

Gain an in‐depth understanding of stakeholders' perceived challenges and expectations across different visitation modalities.

## Methods

3

### Study Design

3.1

We will conduct a descriptive phenomenological study [21, 22]. Descriptive phenomenology is well‐suited to exploring individuals' lived experiences in depth and revealing the essential nature of these experiences through their own perspectives. The Consolidated Criteria for Reporting Qualitative Research (COREQ) [23, 24] checklist will guide the methodological rigor and reporting of this study. A descriptive study design, guided by the stakeholder theory [12], will be employed to explore the knowledge, attitudes, and experiences of healthcare providers, patients, and family members in ICUs regarding in‐person and virtual visitation practices.

### Setting and Sample

3.2

We will use maximum variation purposive sampling to recruit participants with different backgrounds, so that we can collect rich and detailed descriptions of both in‐person and virtual visitation experiences [25, 26]. Before recruitment, researchers will meet with ICU leadership to present the study and obtain informed consent. ICU managers will facilitate the recruitment of eligible healthcare providers, and eligible alert patients will be identified through collaboration with bedside nurses and in‐depth observation. Researchers will assist families with routine ICU visitation, including connecting virtual equipment and instructing on personal protective equipment (e.g., isolation gowns, masks). The researchers explicitly will not engage in any clinical communication, medical decision‐making, or emotional counseling. These interactions will facilitate a good relationship between researchers and patients' families, and help to recruit family members with substantive visitation experiences to obtain detailed insights into in‐person or virtual visitation practices. The estimated sample size will be determined by data saturation [25, 27].

Inclusion criteria for this study are as follows:

For patients: (1) Age ≥ 18 years; (2) ICU stay duration ≥ 48 h; (3) Alert and able to participate in the study during ICU admission or within 24 h post‐ICU discharge; (4) Ability to communicate effectively; (5) Experience of receiving in‐person or virtual visitation; (6) Provision of informed consent for voluntary participation.

For family members: (1) Age ≥ 18 years with the ability to communicate effectively; (2) Experience of participating in ICU visitation; (3) Provision of informed consent for voluntary participation.

For healthcare providers: (1) Currently employed in the ICU during the study period; (2) ≥ 1 year of work experience in the ICU; (3) Familiarity with ICU visitation policies; (4) Voluntary participation and willingness to engage in study procedures.

### Data Collection

3.3

Two researchers of the research team, both experienced ICU nurses with expertise in qualitative research and extensive clinical experience, will conduct in‐depth interviews to explore the experiences of healthcare providers, patients, and families regarding in‐person or virtual visitation practices in ICUs. This approach aims to deeply understand the participants' internal feelings, cognitions, and meanings attributed to their visitation experiences. Prior to the interviews, researchers will explain the study, obtain informed consent, and conduct audio‐recorded interviews in a quiet, comfortable setting of the participant's choice. The study has begun in July 2025 and each interview will last approximately 15–40 min. Given that data collection have already begun, this article is presented as a post hoc protocol. Patient interviews may be conducted in one or two sessions to accommodate potential fatigue. Sociodemographic data of all participants will be collected during the interviews. Non‐verbal cues, such as tone, facial expressions, and gestures, will be documented in real time during and immediately following the interviews.

The interview guide has been developed based on existing literature, team members' clinical expertise, and methodological consultations. Pilot interviews were conducted with 2–3 participants from each stakeholder group (patients, family members, and healthcare providers). The interview guide was refined through pilot feedback and will be further adjusted as data collection proceeds. The interview guide is detailed in Table 1.

**Table 1 hsr272361-tbl-0001:** Interview questions for patients, family members, and healthcare providers.

Patients	Family members	Healthcare providers
Could you elaborate on the most profound emotional experiences you have encountered during ICU hospitalization?	Could you describe your experience of involvement in family visitation? What will you do during these visits?	Could you delineate your specific clinical responsibilities within the current family visitation?
How do you evaluate the current visitation methods?	What difficulties or barriers have you encountered during recent family visitation experiences?	What systemic challenges or operational barriers have you encountered in implementing visitation procedures?
What advantages and limitations do you perceive between in‐person and virtual visitation?	What are your views on in‐person visitation? Please share your perspective on its strengths and limitations, along with the specific reasons behind your evaluation.	How would you assess the efficacy of the current visitation model?
How do you expect to carry out family visitation?	What kind of assistance do you hope to receive during the visitation? Why?	What is your analysis of the comparative clinical value between in‐person visitation and virtual visitation?
What would you like your family to do for you during the visitation?	What are your views on virtual visitation? Please share your perspective on its strengths and limitations, along with the specific reasons behind your evaluation.	What did the family do for the patient during the visitation? What is your opinions of the family's behavior?
	From your perspective, what constitutes an ideal visitation? Please consider the preferred time, frequency, length, number of visitors, and method.	In your view, what are the main risks involved in family visitation, and what are the underlying causes?
		Considering the existing visitation practices, what specific areas do you believe require improvement? Could you tell us your suggestions.

All qualitative interviews will be conducted using mobile device‐embedded audio recording systems to facilitate verbatim transcription and subsequent phenomenological analysis. To ensure ethical compliance, immediately after each interview, the audio file will be renamed with a unique, anonymous study ID (e.g., Case 1, Case 2, Case 3). The interview record will be prefixed with P, F, or H to distinguish patients, family members, and healthcare providers. The researchers will complete the transcription of the audio files within 48 h after the interview ends. The researchers will work under a confidentiality agreement. During the transcription process, the interviewer will conceal all potentially identifiable information of the research participants. Another researcher (not the interviewer) will further detect and remove any potential identifying information when conducting a second verification of the transcribed text. The anonymized transcript will serve as the sole version used for qualitative analysis. The original audio files will be stored separately on a password‐protected, encrypted server accessible only to the principal investigators and will be securely destroyed after a defined retention period.

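### None of the seven healthcare-provider prompts in Table 1 directly asks for the provider's own experience of a visit, so the provider data are likely to be mainly evaluative

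*Protocol article*

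**What the plan says.** The Aims section of the protocol article sets two aims: "Explore the lived experiences and perspectives of stakeholders across different visitation modalities" and "Gain an in‐depth understanding of stakeholders' perceived challenges and expectations across different visitation modalities". The abstract and the Discussion both name healthcare providers among the groups whose lived experience is to be explored. Section 3.1 states "We will conduct a descriptive phenomenological study" and adds a wider scope, "to explore the knowledge, attitudes, and experiences of healthcare providers, patients, and family members in ICUs". Section 3.3 gives the purpose of the interviews for participants in general: "This approach aims to deeply understand the participants' internal feelings, cognitions, and meanings attributed to their visitation experiences". Section 3.4 analyses the transcripts by Colaizzi's method.

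Table 1 in section 3.3 prints the guide, with one column per group. The provider column has seven prompts. It begins with "Could you delineate your specific clinical responsibilities within the current family visitation" and includes "How would you assess the efficacy of the current visitation model". Section 3.3 also says that the guide was piloted in each group, was refined, and will be adjusted further as collection proceeds.

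**The concern.** The design, the first aim and the stated interview purpose all call for participants' own experience and its meaning. The provider column asks mostly about the service: who does what, how well it works, what the risks are and what should change. If providers answer what they are asked, their transcripts will consist largely of service evaluation and professional opinion.

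The study's claim to novelty is at stake. The Introduction says that earlier qualitative work already covers clinical staff's perceptions of visiting frameworks. It places the gap in comparing lived experience across the three groups and the two modalities. If one group supplies mainly appraisals while the other two supply accounts of experience, a difference between groups in the themes may partly reflect a difference in the questions. There would also be a risk of reporting provider opinion under the label of lived experience.

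**Working it through.** No sample size formula or other arithmetic applies. Recruitment follows saturation ("The estimated sample size will be determined by data saturation"), and the check is a count and classification of the printed prompts, set against the aims.

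**Step 1. Classify the provider prompts (Table 1, third column).**
1. Clinical responsibilities in current visiting: duties.
2. Systemic or operational barriers the provider has met: mixed. It asks for first-hand encounters, but only with systems and operations.
3. Efficacy of the current model: evaluation.
4. Comparative clinical value of in-person and virtual visits: evaluation.
5. What the family did during the visit, then the provider's opinion of it: mixed. The first half asks for an account, but of the family's acts.
6. Main risks and their causes: opinion.
7. Areas for improvement: suggestions.

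**Step 2. Count.** Prompts 1, 3, 4, 6 and 7 are purely duties, evaluation, opinion or suggestion: 5 of 7. Prompts 2 and 5 are mixed: 2 of 7. Prompts that directly ask for the provider's own account of a visit, or for its feeling or meaning: 0 of 7.

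**Step 3. Compare the opening prompts.** Patients are first asked about their most profound emotional experiences; that prompt concerns the ICU stay rather than a visit, but it is experiential. Family members are first asked to describe their experience of taking part in visits. Providers are first asked about duties. So two of the three groups open on experience and the provider group does not.

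**Step 4. Check each modality.** Prompt 4 is the only provider prompt that names in-person and virtual visits, and it asks for an analysis of clinical value. No provider prompt asks what either modality was like for the provider.

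**Step 5. Check eligibility (section 3.2).** Patients must have received a visit, and family members must have taken part in ICU visiting. Providers need at least one year in the ICU and familiarity with visiting policy. Personal involvement in visits is not required, so eligibility does not make up for what the prompts leave out.

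**Step 6. Set the prompts against the aims.** Prompts 2, 3, 4, 6 and 7 serve the perspectives half of Aim 1, Aim 2, and the knowledge and attitudes scope of section 3.1. The lived-experience half of Aim 1 and the feelings and meanings named in section 3.3 have no direct prompt in the provider column.

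**The case against.** The strongest reply is that the interviews are in-depth and semi-structured, conducted by nurses described as having qualitative expertise, and directed by a stated purpose that includes feelings and meanings. The printed questions are lead questions. Prompts 2 and 5 can open into experiential accounts, and the guide is expected to change. The aims also cover more than lived experience.

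Much of this stands, and it rules out several stronger readings that a reader might infer:

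- **That all seven prompts ask only for duties, evaluation or opinion.** Prompts 2 and 5 are mixed.
- **That the guide cannot yield provider lived experience.** A skilled interviewer may draw it out, and the guide can be adjusted.
- **That Aim 1 would go unanswered for providers.** Aim 1 includes perspectives, which the prompts do address.
- **That Colaizzi's method cannot use evaluative statements.** Section 3.4 speaks of extracting significant statements and does not limit them to accounts of an experience.
- **That seven prompts in 15–40 minutes leave too little room.** Equal division gives 15/7 = 2.1 to 40/7 = 5.7 minutes per prompt. The six family prompts get 15/6 = 2.5 to 40/6 = 6.7 minutes, which is little different, and a semi-structured interview does not share time equally.
- **That all completed provider interviews are perspectives only.** The transcripts have not been seen, and their content must decide the label.

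The reply does not remove the point. Permission to adjust the guide makes the change easy, but the article does not commit to adding an experiential provider prompt, and the printed guide had already been refined after piloting. Nor is this a detail lost in condensing the protocol: section 3.3 refers the reader to Table 1 for the guide itself, and the comment concerns the prompts printed there.

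**Conclusion.** The point holds in a limited form. None of the seven provider prompts directly asks for the provider's own lived experience of a visit: five are purely duties, evaluation, opinion or suggestion, and two are mixed. As printed, the provider guide is likely to yield mainly evaluative data. That weakens the lived-experience part of Aim 1, the stated interview purpose and the three-group comparison, while perspectives and challenges remain well served.

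The count rests on the printed wording of Table 1. The likely effect on the data is a judgement; it assumes that interviewers keep broadly to the printed prompts and that no unprinted experiential probe is used routinely with providers. This is an inexpensive improvement worth making now, because section 3.3 says collection began in July 2025 and each further provider interview on the current opening adds to the imbalance.

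**What to change.** Under the adjustment that section 3.3 already allows, open provider interviews with an experiential prompt for each modality the provider has taken part in, and ask about duties as a follow-up. For example: *Please describe a recent in-person and/or virtual visit you took part in: what happened, what it was like for you, and what it meant to you.* The remaining prompts can stay.

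For provider interviews already done, report content as lived experience only where the transcript contains a first-person experiential account, and otherwise as perspectives. State in the report when the opening prompt changed.

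The cost is one changed opening and slightly less time for the evaluative prompts. Early provider interviews will have used the old opening, so the provider transcripts will not be fully uniform.

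### Participants can enter with experience of one visitation modality (providers with none) yet are asked about both, and nothing keeps first-hand accounts apart from opinion on an unused modality

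*Protocol article*

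**What the plan says.** **Eligibility (Protocol article, 3.2 Setting and Sample).** The patient criterion is "Experience of receiving in‐person or virtual visitation", so either modality is enough. The family criterion is "Experience of participating in ICU visitation", with no modality named. Providers must currently work in the ICU, have at least 1 year of ICU work, and meet the criterion "Familiarity with ICU visitation policies". None of these requires them to have handled a visit of either kind.

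**Interview guide (3.3 Data Collection, Table 1).** Patients are asked "What advantages and limitations do you perceive between" the two modalities. Providers are asked "What is your analysis of the comparative clinical value between" them. Family members get one item on each modality. The virtual one opens "What are your views on virtual visitation", and both continue "Please share your perspective on its strengths and limitations, along with the specific reasons behind your evaluation". No item depends on the participant having used the modality.

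**Design and purpose.** Section 3.1 justifies the method thus: "Descriptive phenomenology is well‐suited to exploring individuals' lived experiences in depth". The Introduction names the missing comparison of lived experience across modalities as the gap to be filled. The Aims cover lived experience and perspectives, and also perceived challenges and expectations.

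**The concern.** Descriptive phenomenology works from what a participant has actually lived through. A person who has had only in-person visits has no lived experience of a virtual visit to describe, and the reverse holds too. Asked about the other modality, that person can give only an expectation or an opinion.

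That is useful material, but of a different kind. If it is not marked, a theme about virtual visiting could combine accounts from people who used it with assumptions from people who did not. A difference between modalities could then partly reflect familiarity rather than experience. This touches the comparison that the Introduction gives as the study's reason.

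**Working it through.** The study is qualitative and its sample size is set by data saturation, so there is no figure in the plan to reproduce. The check sets the entry criteria beside the questions and then looks for anything that closes the gap.

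**Step 1. Entry criteria against questions.**

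| Group | Least modality experience that meets 3.2 | What Table 1 asks |
|---|---|---|
| Patients | One modality | Contrast both |
| Family members | One modality (any ICU visiting) | Strengths and limitations of each, in two separate items |
| Providers | None stated (policy familiarity) | Comparative clinical value of both |

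In every group an eligible person may be asked about a modality that they have not used. For patients and providers, the contrast item is the only one in the guide that names the two modalities.

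**Step 2. Does anything elsewhere in the article separate the two kinds of answer?**

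- *Sampling (3.2, Discussion).* Maximum variation sampling is meant to yield rich descriptions of both modalities. No modality criterion or target is given, and the attributes named in the Discussion are age, gender and education, followed by an open ending.
- *Guide (3.3).* It may still be adjusted, but no routing by modality is stated.
- *Participant data (3.3).* The data named are sociodemographic. The record prefix (P, F or H) marks stakeholder group, not modality.
- *Analysis (3.4).* Two researchers extract significant statements from transcripts read with the on-site notes, form meaning units and cluster them into themes. No step uses the modality experienced.
- *Rigour (3.6).* Visiting circumstances are to be thickly described. This may capture modality, but it is not a coding rule.

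**Step 3. Can the size be stated?** Let *b* be the share of participants who have used both modalities. The share who have not used at least one is 1 − *b*. The documents do not give *b*, so the values below are assumptions that only show the range.

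- Assume 70% in-person only, 20% virtual only, 10% both. Then 1 − 0.10 = 0.90 have an unused modality. Users of in-person visits are 0.70 + 0.10 = 0.80, and users of virtual visits are 0.20 + 0.10 = 0.30.
- Assume 30% in-person only, 30% virtual only, 40% both. Then 1 − 0.40 = 0.60 have an unused modality. Users of each modality are 0.30 + 0.40 = 0.70.

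In the first case most people asked about virtual visiting have not used it. In the second most have. Nothing in the article says which is nearer the truth.

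**The case against.** The case on the other side is substantial, and much of it limits the point.

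- **Opinion is within scope.** The Aims include perspectives and expectations, and section 3.1 adds knowledge and attitudes. The Table 1 items ask what people perceive or think, and other items ask family members and providers about their own involvement and the barriers they met. This stands: asking about an unused modality is not itself a fault. What remains is that the answers are not kept apart.
- **Sampling already aims at both modalities.** This stands as intent, and the attribute list is open-ended. A reader might infer that modality is left out of the sampling, and the text does not support that. It is simply not named as an attribute.
- **A comparison does not need both modalities in one person.** Correct. In-person users and virtual users can be compared between participants, but only if the analyst knows who used what.
- **The interviews are semi-structured, and exposure would often be known.** The interviewers are ICU nurses, and researchers help families connect virtual equipment. Nothing says that every item goes to every participant. This makes separation feasible, but it is not a stated plan.
- **Providers are likely to have practical involvement.** They are current ICU staff asked about their own duties in visiting. That is plausible, but the criterion does not secure it for each modality.
- **A condensed article may omit coding rules.** True, so silence in section 3.4 is not proof of how such statements will be coded. The point rests on criteria and questions that are both printed and do not match.

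**Conclusion.** The mismatch between section 3.2 and Table 1 is in the printed text for all three groups, and nothing in sections 3.3, 3.4 or 3.6 resolves it. Opinion about an unused modality may therefore be mixed into the lived-experience themes and blur the comparison across modalities. The change is worth making while the guide is still open to adjustment.

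Three stronger conclusions might be drawn, and the documents support none of them:

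- *That hypothetical opinion will be analysed as lived experience.* Section 3.4 does not say so; it only lacks a step to prevent it.
- *That most comparative answers are hypothetical.* Any such percentage depends entirely on an assumed share with both modalities.
- *That the less-used modality is described mainly by people who never used it.* This fails under a plausible split, such as the second case above.

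The size is unknown. The verdict assumes only that some participants will have used a single modality, which the criteria permit, and that some of them will be asked about the other.

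**What to change.** 1. **Record exposure.** For each patient and family member, note in-person only, virtual only or both. For each provider, note which modalities they have handled, if any. Name this as a maximum-variation attribute in section 3.2.
2. **Route the remaining interviews.** Ask experience questions about modalities the participant has used or handled. Questions on an unused modality can stay, with the answers treated as expectation.
3. **Add a coding rule to section 3.4.** Within the Colaizzi analysis, code first-hand accounts and expectations separately. Lived-experience themes and the modality comparison then rest on first-hand accounts, either between participants or within those who used both. Expectations serve the second aim.
4. **Completed interviews.** Data collection began in July 2025 and finished interviews cannot be re-routed. Assign exposure from transcripts and on-site notes where possible, and report where it could not be established.

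The cost is one data field, conditional questions in a guide that is still adjustable, and one coding rule. It brings slightly more screening and coding work, and exposure data for the early interviews will be incomplete.
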